### 3.1 Niger

Historically, Niger has been hyperendemic for trachoma. Most individuals in the country received oral azithromycin in the mid 2000s, but the program has lapsed over the last 3 years. There is evidence that clinical trachoma has returned in some areas since the last treatment. The prevalence of clinically active trachoma in Matameye district has been estimated, and the Programme National de Lutte Contre la Cécité (PNLCC) and Carter Center have determined that retreatment is warranted. Previous data suggest at least three rounds of mass treatment will be necessary.

### 3.2 Tanzania

In Tanzania, trachoma is prevalent largely throughout the country. The Dodoma region had the highest rates of trachoma in Tanzania, and the Tanzania National Trachoma Control Program started its activities in that region. Kongwa is a district in Dodoma, comprised of largely subsistence farmers. The Kongwa Trachoma project in collaboration with Johns Hopkins University was started in 1986 to document the burden of disease, and has since been the field site for studies of trachoma, including development of diagnostics, immunological studies, and clinical trials of face washing, fly control, and azithromycin use in communities. In this setting, program activities over the last eight

---

 Report of the Eighth Meeting of the WHO Alliance for the Global Elimination of blinding Trachoma. *Report of a WHO Working Group*. 2004; World Health Organization Geneva Switzerland. WHO/PBD/GET/04.2

years have reduced infection and disease from greater than 50% to 10%-30%, but at a slow pace. We expect that with more rigorous coverage and surveys to stop mass treatment when warranted, we can improve cost effectiveness of the programs. The Kongwa Trachoma project with Johns Hopkins University has been an integral part of the Tanzania National Trachoma Control Program, conducting surveys to document the effect of the program in regions all over Tanzania.

### **3.3 The Gambia**

In The Gambia, there has been a decline in the national prevalence of active trachoma in recent years (from 20% to 7% in national surveys in 1986 and 1996: adjusted to 1-9 age group) but a survey in 2006 showed that substantial parts of Lower River Division (LRD) and North Bank Division (NBD) still have more than 10% prevalence of active trachoma in children under 10, and there is evidence that active trachoma persists at potentially blinding levels in foci elsewhere in the country. The program has identified 11 rural districts (rural districts vary from 5-20,000 population) and a total population of 150,000 who need mass treatment based on the WHO criteria. There has been a longstanding relationship between the National Eye Care Program and the LSHTM trachoma research group based at the Medical Research Council Laboratories which has led to a series of studies focused both on diagnostic and immunological studies in trachoma and operational research for trachoma control.

## Chapter 4: Randomization Arms and Sample Size

---

### 4.1 Overview

We propose to randomize communities in a 2 X 2 factorial design within each of the three countries. Communities will be randomized (minimum 16 in each arm) to two different coverage targets (80%-89% versus  $\geq 90\%$ ) for three years of mass treatment. In Niger, communities will be further randomized to annual mass azithromycin distribution for everyone versus every 6 month distribution in children ages twelve and under. In The Gambia and Tanzania, communities will be randomized to yearly mass treatment versus yearly mass treatment if warranted by the infection /disease rates. We will evaluate the efficacy of guiding further mass treatment according to a laboratory test for Chlamydia or WHO guidelines. Where we estimate communities have infection rates less than 5% in sentinel children, or TF rates less than 5%, the community will be “graduated” from further mass treatment and followed for up to three years to look for evidence of re-emergent infection and disease. If rates of infection return at the 12 or 18 month survey to 20%, then mass treatment will again be initiated as clearly the stopping rule will have failed.

Sentinel children age five years and younger will be randomly selected from each community based on census of the community, as cross sectional samples of the rates of trachoma and infection. The census will be updated each year, and villages monitored at baseline, 6, 12, 18, 24, 30, and 36 months for infection and clinical disease. The three-year study is in accord with the WHO guidelines for three years of annual mass treatment followed by a re-survey to determine need for further treatment.

### 4.2 Randomization Arms

The basic structure of the trial is shown in Table 1. In this 2 X 2 factorial design, communities in each location will be randomized into four treatment arms, but these arms will differ by country. All communities will receive mass treatment with azithromycin at baseline. At present, recommended coverage of the community is 80% or better. We propose to evaluate the effect of two coverage targets, (estimated in children age 0 to 9 years old). The two arms would have 1:1 randomization at community level to one of two coverage targets: 80% to 89% coverage (reasonable program targets) and  $\geq 90\%$  (enhanced program coverage, requiring additional time and resources). All countries will be participating in the randomization arms for coverage, in order to determine the incremental effectiveness of extra effort in coverage in reducing infection and disease.

The second component of the antibiotic trial is frequency of administration of mass treatment. We propose two frequencies of mass antibiotic administration, yearly for everyone in the community (The Gambia, Niger, and Tanzania) and every six months for children ages twelve and under (Niger). The rates of disease and infection within Tanzania and The Gambia are not

hyperendemic, and the resources to mass treat more than yearly cannot be justified. Research in Tanzania has shown that re-emergence across households takes about one year, suggesting this interval is reasonable. Therefore, for communities within Tanzania and The Gambia, we propose an alternative frequency regime: communities receiving yearly mass treatment will be further randomized to two arms: yearly mass treatment every year for three years (similar to the Nigerien arm), versus an arm that allows mass treatment cessation if the community achieves our clinical or infection goals. These goals are a prevalence rate in 0-5 year olds of less than 5% trachoma (defined as TF rates less than 5%) or 5% infection (defined as laboratory positive rate of less than 5%).

**Table 1: Treatment coverage and frequency randomization arms by country**

| Country    | Frequency of mass treatments                              | No. of communities treated | Coverage                         |
|------------|-----------------------------------------------------------|----------------------------|----------------------------------|
| Niger      | 3 Annual mass treatments                                  | 12                         | 80 – 89% tx coverage $\Upsilon$  |
| Niger      | 3 Annual mass treatments                                  | 12                         | $\geq 90\%$ tx coverage $\Omega$ |
| Niger      | 6 Biannual mass treatments to children ages 12 or younger | 12                         | 80 – 89% tx coverage $\Upsilon$  |
| Niger      | 6 Biannual mass treatments to children ages 12 or younger | 12                         | $\geq 90\%$ tx coverage $\Omega$ |
| Tanzania   | 3 Annual mass treatments                                  | 8                          | 80 – 89% tx coverage $\Upsilon$  |
| Tanzania   | 3 Annual mass treatments                                  | 8                          | $\geq 90\%$ tx coverage $\Omega$ |
| Tanzania   | Stopping rule (Max. 3 Annual mass treatments)*            | 8                          | 80 – 89% tx coverage $\Upsilon$  |
| Tanzania   | Stopping rule (Max. 3 Annual mass treatments)*            | 8                          | $\geq 90\%$ tx coverage $\Omega$ |
| The Gambia | 3 Annual mass treatments                                  | 12                         | 80 – 89% tx coverage $\Upsilon$  |
| The Gambia | 3 Annual mass treatments                                  | 12                         | $\geq 90\%$ tx coverage $\Omega$ |
| The Gambia | Stopping rule (Max. 3 Annual mass treatments)*            | 12                         | 80 – 89% tx coverage $\Upsilon$  |
| The Gambia | Stopping rule (Max. 3 Annual mass treatments)*            | 12                         | $\geq 90\%$ tx coverage $\Omega$ |

$\Upsilon$  Target of 80-90% azithromycin treatment coverage in each community

$\Omega$  Target of greater than 90% azithromycin treatment coverage in each community

\*The stopping rule states that mass treatment will be stopped if trachoma infection is less than 5% of the sample. There is a maximum of three annual mass treatments.

•100 children per community are randomly selected to represent the village prevalence of infection, disease

### 4.3 Communities and Sentinel Children

In order to determine the impact of our treatment arms on trachoma and infection, we will randomly sample a sentinel group of up to 100 children within randomly selected communities. *We define communities as the smallest population unit for which health services are organized and trachoma control programs are implemented.* These communities vary in size between countries. In Niger, we will use Grappes, comprised of 250- 600 people, as communities. In The Gambia, we will use Census Enumeration Areas, of population size 600-800 as communities. In Tanzania, we will use mtaas or clusters of mtaas, which average around 1200 population. As described below, we plan to have 8 communities in each cell of the Tanzanian arms, and 12 communities in each cell of the Nigerien and The Gambian arms. We need multiple communities to have a stable estimate of the impact of the treatment arm.

We also need a large enough sample **within** the communities for The Gambia and Tanzania, in order to be able to determine if mass treatment is to cease, based on our infection and disease rules for stopping. The universe of children being sampled differs for each of the country settings, as it relates to the size of the community. In Tanzania, of the potentially 16,000 children who form the universe of the sample, 3200 will be randomly selected, or one in five. In The Gambia, 48 Census Enumeration Areas (CEA) will be randomly selected of the 114 to serve as sentinel communities. With about 700 persons total and 175 children in the eligible age range, the total universe for this sample is 8400 children. 4800 children will be randomly selected at each survey, for a slightly higher than 1/2 chance of selection. In Niger, the study area is comprised of 6 Centre de Santé Intégrés (CSI) or integrated health centers composed of 235 grappes (roughly comparable to a village with an

average size of 375 people). 48 of these grappes were randomly selected to serve as study communities (8 grappes from each of the 6 CSI), with up to 100 children and 40 randomly selected adults included in each round. Note, that there is no stopping rule in Niger, and thus a sample size smaller than 100 children is not an issue.

For this trial, we propose to monitor the changes in prevalence and infection over time according to treatment arm. For this, simple cross-sectional samples of up to 100 children ages 0 to 5 years within the community at specified times are sufficient. This sample will enable us to determine the effect of treatment after each round, and if treatment is to be stopped in the communities of The Gambia and Tanzania. This sample will not be followed longitudinally, and at each sampling time, a new random sample will be drawn. To support the sampling, a census update will be performed yearly.

#### **4.3.1 Details on Randomization for Niger**

Figure 1 illustrates the sampling plan for Niger. We will be working in the Matameye department of the Zinder Region. We will randomize at the grappe level.

For randomization, we stratified based on geography and endemicity. As indicated above, we began with six CSIs. Each of these six CSIs contributed 8 grappes to the study—with two grappes per CSI allocated to each of the 4 arms (for a total of twelve grappes in each of four arms, or 48 total). Moreover, we ranked the eight grappes from each CSI by clinical activity in 0-5 year old children. The top four of these were considered higher prevalence, and the lower four were considered lower prevalence. When randomizing, one higher prevalence grappe from each CSI was randomized to each treatment arm, and one lower prevalence grappe was randomized to each treatment arm. Finally, each study arm has one randomly chosen grappe intended for detailed longitudinal follow-up.

Each of the 48 grappes will have a complete census; the census will be used to randomly select children as well as provide the basis for data on treatment according to randomization into treatment arm. After the census, we will have a complete listing of all children five years or younger. One hundred of these children will be randomly selected, by assigning each child a random number and choosing the children 0-5 years associated with the lowest 100 numbers (or all children if a grappe has less than 100 in this age group). A second group of 20 children will be randomly selected as a substitution group if not all children from the first group of 100 are available. If a child on the list of 100 is not examined, the reason will be recorded (anticipated reasons include: moved to nearby grappe, moved to Maradi, Zinder, or Nigeria, absent for the day, absent more than 1 month, sick, or guardian refused). In addition, 40 adults (age 15+) will be randomly selected for monitoring at each collection.

[figure not shown]

### 4.3.2 Details on Randomization for Tanzania

Figure 2 illustrates the sampling plan for Tanzania. We will be working in the district of Kongwa Tanzania, which contains 67 villages. Of these villages, 10 are either large towns with low trachoma rates or villages known to have trachoma rates that are less than 10%. The remaining 57 villages are eligible for this trial. We will have some preliminary data on trachoma rates (data from other surveys past 2005) on all of them by end of February, and plan to identify the mtaas or clusters of mtaas within each village and stratify them into groups by rates of trachoma. The overall distribution of villages into these categories will dictate the distribution in each of the arms of the trial. We plan to use a SAS macro for constrained randomization, for this community randomized design. This approach reduces the likelihood of a bad randomization outcome by balancing on baseline trachoma as co-variables. We plan to randomly select then 9 communities in each arm, one to serve as an alternate in case a community selected is either not eligible or refuses to participate.

Each of the 2 X 2 cells in Figure 2 are marked as “A, B, C, or D” and each will have eight communities randomly assigned until 32 communities are selected for the trial using the allocations that meet the balance criteria.

Each of the 32 communities will have a complete census carried out; the census will be used to randomly select children as well as provide the basis for data on mass treatment according to randomization into treatment arm. After the census, we will have a complete listing of all households with at least one child age five years or younger. One hundred of these households will

be randomly selected, by assigning a random number to each household and using the first 100 numbers. Within each household, we will also assign random numbers to each child age five years and younger and select the child with the lowest random number. This avoids clustering at the household level. In Tanzania, the communities are large and have on average 240 households, and 85% contain a child in this age range, so we anticipate no problem in having ample households for the sample. In the event that there are fewer than 100 eligible households, we will then randomly pick the households in which two children age 5 years and younger are selected, and note to adjust for household clustering. We plan to randomly select 110 households in total, with the final ten households held in reserve in case we are unable to examine the first 100 children. We need 100 children at each examination, and we will make considerable effort to find the child randomly selected in the first 100 households, but if they are known to be gone from the community over the examination period, or the household cannot be located over two visits at two different times, then a child will be selected off the alternate list.

[figure not shown]

### 4.3.3 Details on Randomization for The Gambia

Figure 3 illustrates the sampling plan for The Gambia. We will randomize, at district level, 60,000 total population, about 15,000 in each arm, for antibiotic treatment coverage. These communities will be treated with mass antibiotic yearly as described in the randomization section above, or allocated to stopping rules. We will work in the contiguous rural Gambian districts of Lower Badibu (est. 2008 population 15,556) Central Badibu (est. 2008 population 14,964), Foni Bintang Karanai (est. 2008 population 18,866) and Foni Kansala (est. 2008 population 15,394), which have all been identified in the Gambia's national trachoma control plan as requiring annual mass treatment for three years.

We will use a random number generator program to assign each district to a 2 X 2 cell in Figure 3 marked as “A, B, C, or D”. Within each district the effects of each strategy will be assessed in 12 of the 30 census enumeration areas, which will be randomly chosen. A census enumeration area contains variously several small hamlets, one medium sized village or represents a subdivision of a large village. In these 12 EAs per district a census will be carried out; and the census will be used to randomly select children as well as provide the basis for data on mass treatment according to randomization into treatment arm. After the census, we will have a complete listing of all households within each EA, and will be able to identify those containing at least one child age five years or younger. In 9 EAs per district we shall take a 25% sample of children age 5 and under, by selecting households from the list at random until the sample includes 100 children age 5 and under. To ensure that a number of 100 is reached we will randomly select a further 10 households to serve as reserves. In 3 randomly chosen EAs we will sample all children 0-9 as described in the ancillary study.

[figure not shown]

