#### **4.4.2 Children**

We chose a sample size of 100 children per community specifically for the Tanzanian and Gambian arms, where we need sufficient numbers of children to determine with precision if disease has fallen to less than 5%. At the same time, we balanced concerns for costs and survey difficulties if this methodology is to be used by country programs to decide if mass treatment can be stopped. With 100 children in the sample, if zero children have infection, the upper 95% confidence limit of the estimated prevalence is less than 5% (3%). For example, if one child in the sample has infection, then mass treatment will not be stopped, even though the estimate of the mean is 1%, as we cannot be 95% certain that the true prevalence is not above 5%. We cannot power the study for infection below 1%, as that would require over 3 times the sample size (368 children), and such a size would be prohibitively expensive in terms of laboratory testing and follow-up time. However, with our sample size of 100 if even one child has infection, we know the estimate is 1% with a 95% upper confidence bound of 5.4%. We recognize this is a conservative approach, but we are strengthening the likelihood that the true value is below 5% according to the upper confidence limit.

---

 Feiveson AH. 2002. Power by simulation. STATA Journal 2:107-124

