#### **12.4.1.2 MASTER SURVEY LIST**

The Master Survey List is a copy of the original census document. In the 3 'longitudinal' CEAs all children 0-9 are chosen, and in the 9 'sample CEAs 100 children aged 0-5 are randomly selected, together with 10 reserves. The registration form then contains the full spelling of each individual's name, as well as their age, gender, and household number. A new randomized Master Survey List is generated for each CEA at each collection visit and is used for both mobilization (the day before collection is scheduled) and registration.

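### The Gambian stopping sample is described both as a draw of households and as a draw of children, and the 3% upper limit for zero of 100 is established only for the second

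*Protocol*

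**What the plan says.** **The Gambian draw.** Section 4.3.3 lists households from the census in 12 EAs per district. In 9 of them "we shall take a 25% sample of children age 5 and under", carried out "by selecting households from the list at random until the sample includes 100 children age 5 and under", and a further 10 households are held in reserve. In the other 3 EAs all children aged 0-9 are examined. Section 12.4.1.2 describes the master list for the same 9 EAs differently: "100 children aged 0-5 are randomly selected, together with 10 reserves".

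**The sampling fraction.** Section 4.3 states: "With about 700 persons total and 175 children in the eligible age range, the total universe for this sample is 8400 children". It then takes 4800 of them, a chance of selection a little above one half.

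**The justification for 100 children.** Section 4.4.2 sets this number specifically for the Tanzanian and Gambian arms and says that "if zero children have infection, the upper 95% confidence limit of the estimated prevalence is less than 5% (3" per cent). Section 8.6 applies the stopping rule directly to the count in the sample.

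**The other countries.** In Tanzania (4.3.2) one child is taken per selected household: "This avoids clustering at the household level". In Niger (4.3.1) children are drawn individually. Section 5.2 accepts several children per household in small communities and leaves the clustering to the analyses.

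**The concern.** The two Gambian descriptions are different designs. Filling a sample to 100 by household means that siblings and other children sharing a cooking pot enter together. If infection runs in households, 100 such children carry less information about the EA than 100 children drawn one by one. The limit in 4.4.2 belongs to the second design.

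One normally deals with clustering in the analysis. Here the count is itself the decision: once zero positives have led to a stop, no later standard error changes that. The protocol recognises household clustering and removes it in Tanzania, but leaves it open in the other country where the count triggers stopping. At stake is whether a zero count supports the same certainty in both countries, and whether field teams know which list to draw.

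**Working it through.** **1. The plan's own figure.** For 0 of 100 independent children, the one-sided 95% limit is 1 − 0.05^(1/100) = 2.95%, which is the stated 3%. (The 5.4% for 1 of 100 and the 368 children in the same section reproduce only as two-sided figures. On that basis 0 of 100 gives 1 − 0.025^(1/100) = 3.6%.)

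**2. The sampling fraction.** 100/175 = 57%, and 4800/8400 = 57%. A 25% sample that yields 100 children would need 100/0.25 = 400 eligible children per EA. Since 175/700 is also 25%, the phrase may be a slip for the share of residents in the age range; the protocol does not say.

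**3. Household draw, binomial basis.** Inputs not in the protocol, so assumed: m eligible children per household and intra-household correlation ρ. DEFF = 1 + (m − 1)ρ; n_eff = 100/DEFF; limit = 1 − 0.05^(1/n_eff).

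| DEFF | n_eff | limit |
|---|---|---|
| 1.0 | 100 | 2.95% |
| 1.2 | 83.3 | 3.5% |
| 1.5 | 66.7 | 4.4% |
| 2.0 | 50 | 5.8% |

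The limit reaches 5% at n_eff = ln 0.05/ln 0.95 = 58.4, so at DEFF = 100/58.4 = 1.71 (1.39 if two-sided). The matching correlation is 0.71/(m − 1): 0.71 for m = 2, 0.36 for m = 3, 0.24 for m = 4, 0.18 for m = 5. An exact beta-binomial calculation is milder: m = 3 with ρ = 0.5 gives 4.8%, and m = 4 with ρ = 0.5 gives 5.6%.

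**4. The EA is finite.** Step 3 treats the EA as unlimited, whereas the plan takes 100 of about 175.

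- *Children drawn individually.* With 3 infected, P(none found) = (75·74·73)/(175·174·173) = 0.077; with 4 infected it is 0.032. The limit is 3/175 = 1.7%.
- *Households drawn, complete clustering (ρ = 1).* In each row below, 3 infected households are the most that leave P(none found) above 0.05.

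| m | households in EA | drawn | P(none), 3 infected | limit |
|---|---|---|---|---|
| 2 | 88 | 50 | 0.077 | 6/175 = 3.4% |
| 3 | 58 | 34 | 0.066 | 9/175 = 5.1% |
| 4 | 44 | 25 | 0.073 | 12/175 = 6.9% |
| 5 | 35 | 20 | 0.070 | 15/175 = 8.6% |

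- *Partial clustering.* Beta-binomial households were simulated for m from 2 to 5 and ρ from 0.1 to 0.6, looking at EAs with true prevalence 4.5-6%. The chance of finding none stayed below 5% in 23 of 24 settings; the exception was m = 5 with ρ = 0.6, at 6.3%. At m = 4 with ρ = 0.3 it was 0.8%.

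**5. If the 25% were right.** With 400 eligible children, individual drawing gives 2.5%. Complete household clustering gives 5.0% (m = 2), 6.8% (m = 3) and 9.0% (m = 4). The conflict over the fraction therefore also decides how much protection the finite EA gives.

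**The case against.** The best reply is that the sample is more than half of each EA, so a zero count is strong evidence however the children are reached. Step 4 bears this out: the starting point is 1.7%, and moderate clustering leaves the limit under 5%. It can also be said that 12.4.1.2, the operational list procedure, already draws children; that 4.3.3 never says outright that every eligible child in a drawn household is taken; that 3 of 12 EAs are unaffected; and that only the stopping-rule arms use the count. All of this stands. It limits the size of the problem, but it does not settle which draw is meant or supply a limit for the household draw.

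A reader might infer more, and the documents do not support it:

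- *That the assurance of under 5% fails in The Gambia.* This needs a household size and a correlation that the protocol does not give, and on its own EA size it needs very strong clustering.
- *That a 25% sample means 44 children, with a limit of 6.6% for 0 of 44.* Every statement of the sample size is 100; the 25% is a wrong description.
- *That the chance of missing 5% prevalence is 18%.* That figure puts 9 infections in 2 households; with 4 children each, only 8 fit.
- *That a zero count at a true 3% is an error.* The goal is prevalence below 5%, so it is not.

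**Conclusion.** The point holds as a conflict in the documents and an unsupported figure. Sections 4.3.3 and 12.4.1.2 give different units of draw, and 4.3.3 and 4.3 give different sampling fractions (25% against 57%). The 3% limit is correct for independent children but is not established for the household draw of 4.3.3, and the raw count cannot be adjusted afterwards. It applies to 9 of 12 EAs per district and affects the stopping decision in the stopping-rule districts.

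The size is uncertain: the limit passes 5% above a design effect of 1.71 on the plan's binomial reasoning. In a 175-child EA it passes 5% only when infection is concentrated in very few households of 3 or more children. Both statements rest on assumed household sizes and correlations, and on reading 4.3.3 as taking all eligible children in each drawn household. This should be fixed, at moderate priority.

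**What to change.** Align 4.3.3 with 12.4.1.2: from the EA census list of children aged 0-5, draw 100 children and the reserve children individually at random, as Niger does. Delete the 25% and the reserve households. A simple random draw from a complete list gives the 1.7% limit of step 4 whatever the household correlation, so the stated 3% then covers The Gambia.

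If the household draw is kept for field reasons, say in 4.4.2 that the 3% limit assumes independent children and is not established for The Gambia, and correct 12.4.1.2 and the sampling fraction to match.

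The cost is one paragraph. The census already lists the children by household. The one practical drawback is that the sample is spread over more households, so more families have to be notified.
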